**Methods:**

This trial is a prospective, multicenter, randomized, double-blind, placebo-controlled, superiority trial aimed at evaluating the efficacy and safety of YQFM in reducing the disability rate in patients with acute hypoperfusion stroke within 90 days. We will recruit 480 patients with AIS within 48 h of symptom onset from 24 hospitals, who have large atherosclerosis, systolic pressure ≤ 155 mmHg, and an NIHSS score of 4–18. Eligible patients will be randomly assigned to receive either YQFM or 0.9% NaCl injection once daily for 10 days and will be followed up until the 90th day after stroke onset.The primary outcome will be the proportion of patients with mRS ≤ 2 at 90 days after patient recruitment. Secondary outcomes will include the proportion of early neurological deterioration at 7 days, patient self-reported outcomes and the syndrome score at 10 days, MMSE scale and BI scale at 90 days.During the trial, adverse events will be recorded. These data will be analyzed according to the predetermined statistical analysis plan.

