### Secondary outcomes

Secondary outcomes will include the following: the percentage of early neurological deterioration (defined as an increase of 2 or more points in the NIHSS score at D3 compared to baseline), the degree of neurological deficiency (measured by the change in the NIHSS scale between baseline and D10), patient self-reported outcome (measured by the change in the PRO scale between baseline and D10), change in Traditional Chinese medicine syndrome (evaluated using a stroke syndrome elements scale at baseline and D10), degree of disability (evaluated by the distribution of mRS scores at D30 and D90), proportion of patients capable of performing daily living activities (evaluated by BI scale scores at D30 and D90), mental status assessment (evaluated using MMSE scores at D90), recurrence rate of cerebrovascular events and stroke-related mortality within 90 days of onset, and incidence of important vascular events within 90 days.

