### Sample size calculations

Referring to the distribution of the mRS at the 90 days after stroke onset in the Chinese National Stroke Registry Study, it was found that the proportion of mRS ≤ 2 was 64.6%. In the control group, the percentage of participants with mRS ≤ 2 was 65%, while in the intervention group, the proportion would be 76.5%.The sample size was calculated using PASS 21.0.2.The difference test between the two sample rates was used to calculate the sample size, and a 1:1 design was conducted at the testing level α=0.05 (bilateral) and 1-βß0.8. Considering a 20% dropout rate, each group should include 240 cases, bringing the total number of cases to 480.

$$n = {{2pq{{\left( {z{{\kern 1pt} _\alpha } + {z_\beta }} \right)}^2}} \over {{{\left( {p1 - p2} \right)}^2}}}$$

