### Data analysis

The missing data are processed by multiple interpolation. If the primary efficacy index is missing, the previous result is carried forward according to the intentionality analysis.If there is a valid value carried forward after randomization, the last observation is used for carry-over.

The main efficacy measure (the percentage of patients with mRS ≤ 2 ) will be compared and analyzed using the chi-squared test. The statistician will perform covariate adjusted analyses and covariate unadjusted analyses. Subgroup analyses will include sex, age, systolic blood pressure, and the baseline NIHSS score.

For dichotomous outcomes, such as the percentage of BI ≥ 90, distribution of mRS scores, proportion of early neurological deterioration, and recurrence rate of stroke, we will use the chi-squared test or Fisher’s exact test to compare the distribution of patients between the two groups.Logistic regression is utilized to estimate the 95% CI. For continuous variables, including neurological function scores, MMSE scores, PRO scale, cerebral blood flow, such as changes from baseline to treatment endpoints, Student’s t-test or Wilcoxon rank-sum test is employed to analyze the differences between the two groups.Survival data will be estimated using the Kaplan-Meier method, survival curves will be plotted, and efficacy will be evaluated using log-rank tests.

According to the safety set data, statisticians compare and analyze the differences in the incidence of adverse events, major adverse events, and liver and kidney dysfunction, as well as routine blood and urine tests between the two groups. For most safety data, Cox proportional-hazards models are used to estimate the hazard ratios between the two treatment groups.

When 50% of the subjects have completed the study, an interim analysis will be conducted. The continuation or suspension of the study is determined according to the analysis results. If the analysis results indicate that valid results cannot be obtained, the study will be terminated immediately. The study will continue if data analysis suggests that efficacy may be achieved at the end of the study.

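### The Barthel Index is cut at 90 and compared by an unadjusted chi-squared or Fisher test; a baseline-adjusted responder analysis plus a full-scale BI analysis would probably use the collected data better

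*Protocol article*

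**What the plan says.** Four places in the protocol article bear on this.

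- **Abstract, Methods:** the secondary outcomes include "MMSE scale and BI scale at 90 days".
- **Secondary outcomes:** the endpoint is the "proportion of patients capable of performing daily living activities (evaluated by BI scale scores at D30 and D90". This is a proportion. No threshold is given here.
- **Data analysis:** the threshold appears in "For dichotomous outcomes, such as the percentage of BI ≥ 90". For this group of outcomes, "we will use the chi-squared test or Fisher’s exact test to compare the distribution of patients between the two groups". The next sentence adds that "Logistic regression is utilized to estimate the 95% CI". Other scales are handled as scores: "For continuous variables, including neurological function scores, MMSE scores, PRO scale, cerebral blood flow, such as changes from baseline to treatment endpoints" go to a t-test or Wilcoxon test. BI is not named in that list.
- **Appendix C, visit flow chart:** BI is recorded at Day 1, Day 30 and Day 90.

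The paragraph on the primary outcome also states that "The statistician will perform covariate adjusted analyses and covariate unadjusted analyses". The covariates are not named.

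**The concern.** Cutting a graded score at one point treats all patients on the same side as equal. A patient who ends just below 90 counts the same as one who ends far below it, and a patient at 90 the same as one at the top of the scale. Improvement that does not cross 90 is invisible to the test. The chi-squared and Fisher tests also take no covariates, so the Day 1 BI cannot sharpen the comparison, although it is collected and probably correlates with the later scores.

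The primary outcome is already a binary functional cut (mRS ≤ 2). A second unadjusted binary cut on a related scale adds less than the full BI score could. At stake is information on one secondary endpoint. The primary analysis is not affected.

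**Working it through.** **The plan's own figure.** The article states no rate, SD, effect or power for BI, so there is no BI figure to reproduce. The only sizing is for mRS ≤ 2: 65% v 76.5%, "α=0.05 (bilateral"), 80% power, 20% dropout, 240 per group. The printed formula with p = 0.7075 gives about 246 per group before dropout, so 240 after dropout does not reproduce. That is a separate matter. Here the figures serve only as a borrowed scenario.

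**Inputs**
- From the article: two-sided α 0.05; 240 per arm; 20% dropout, so 240 × 0.8 = 192 evaluable per arm.
- Assumed: 65% v 76.5% applies to BI ≥ 90; the benefit is a common shift on a latent normal scale; BI has 11 ordered levels; 30%, 45% or 60% of controls reach the top level; Day 1 BI correlates 0.3 to 0.5 with the outcome.

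**Step 1. Power of the stated test.**

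z = [(p2 − p1)√n − 1.96√(2p̄q̄)] / √(p1q1 + p2q2)

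- √(2 × 0.7075 × 0.2925) = 0.6433, and 1.96 × 0.6433 = 1.261.
- √(0.65 × 0.35 + 0.765 × 0.235) = 0.638.
- n = 192: (0.115 × 13.856 − 1.261) / 0.638 = 0.52, power about 70%.
- n = 240: (0.115 × 15.492 − 1.261) / 0.638 = 0.82, power about 79%.

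**Step 2. Power of a full-scale analysis, benefit spread over the scale.** The latent shift that moves 65% to 76.5% is probit(0.765) − probit(0.65) = 0.722 − 0.385 = 0.337 SD. Simulation with 192 per arm:

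| Controls at top level | Chi-squared at 90 | Wilcoxon, full score | Rank ANCOVA with Day 1 BI (r = 0.5) |
|---|---|---|---|
| 30% | about 70% | 87% | 94% |
| 45% | about 70% | 84% | 91% |
| 60% | about 70% | 77% | 85% |

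Repeat runs put the rank test between 75% and 87%, and rank ANCOVA as low as about 79%. Logistic regression on BI ≥ 90 with Day 1 BI as covariate gives about 71 to 78%, a modest gain over chi-squared with the endpoint unchanged.

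**Step 3. Other assumptions.**
- A 21-level BI with floor and ceiling and a uniform shift: the cut loses about 8 to 15 points against Wilcoxon, but only about 1 to 12 against the t-test.
- A latent normal score without ceiling, 40 to 70% of controls meeting the cut: when the full score has 80% power, the cut has 54 to 60%, a loss of 20 to 26 points.
- Benefit confined to patients moving from 60–85 to 90 or above, 192 per arm: chi-squared 45 to 63%, Wilcoxon 22 to 27%. The ordering reverses.

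The result therefore runs from a loss of up to about 26 points to a clear advantage for the cut, depending on where on the scale the benefit falls.

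**The case against.** The strongest reply is that the test fits the endpoint. The Secondary outcomes section defines a proportion, a proportion needs a threshold, and chi-squared or Fisher is a normal way to compare one. The abstract's mention of the BI scale may only name the instrument. MMSE and PRO are defined there by scores or change, so treating them differently is consistent. This stands: the responder endpoint is legitimate and should stay. It does not show that an unadjusted test is the best way to analyse it, or that the full score has nothing to add.

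Four stronger readings are tempting, and the article does not support them.

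- *The Day 1 BI is never used.* Logistic regression is planned for the intervals, and adjusted analyses are planned in the primary-outcome paragraph, all with covariates unnamed. Day 1 BI is neither included nor excluded. Only the named test leaves it out.
- *The cut at 90 is unjustified.* A reason may stand in the full protocol or the analysis plan, which are not shown. Its absence from a condensed article is no finding.
- *BI is the trial's only direct measure of daily living.* The primary outcome itself defines mRS ≤ 2 as relative independence in daily living, and degree of disability is assessed by the mRS distribution.
- *The cut costs a known number of power points.* No BI distribution or effect is given, so no single figure follows from the article.

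The outcome lists in the Data analysis section are also open-ended, so a score analysis of BI is not ruled out. It is simply not stated.

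**Conclusion.** The point holds as a cheap improvement to one secondary outcome. The article reduces a graded score measured three times to one yes/no cut and names a test that takes no covariate. If the mRS rates carry over to BI ≥ 90, 192 patients per arm are evaluable and the benefit is spread across the scale, power is about 70% for chi-squared and about 75 to 87% for a rank test on the full score, a difference of 5 to 17 points. Day 1 BI adds further power at an assumed correlation of 0.3 to 0.5. If the benefit sits at the cut, nothing is lost and the binary test can win. That is a reason to have both analyses, not to replace one with the other. Nothing here affects the primary outcome or the trial's size.

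**What to change.** Before unblinding, amend the Data analysis section or the statistical analysis plan as follows.

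1. Keep the proportion with BI ≥ 90 at Day 30 and Day 90 as the responder endpoint. Analyse it by logistic regression with treatment and Day 1 BI in place of the unadjusted chi-squared or Fisher test, and report the odds ratio with its 95% CI.
2. Add a pre-specified full-scale BI analysis at both visits: proportional-odds regression, or rank ANCOVA, with treatment and Day 1 BI. Report the common odds ratio, or the probability of a better score, with its 95% CI.
3. State that the responder result remains the defined endpoint and the full-scale result supports it, so that the choice between them is not made after seeing the data.

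The cost is a sentence or two of text. No new visits, patients or measurements are needed. The downside is a summary measure less intuitive than a percentage, and a proportional-odds check if that model is chosen.

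### The mRS distribution at D30 and D90 is an ordered secondary outcome, but the analysis section calls it dichotomous and gives it a test that cannot use the order

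*Protocol article*

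**What the plan says.** The Secondary outcomes section of the protocol article lists "degree of disability (evaluated by the distribution of mRS scores at D30 and D90". This is separate from the primary outcome, the proportion with mRS ≤ 2 at D90, which has its own sentence in Data analysis: "The main efficacy measure (the percentage of patients with mRS ≤ 2 ) will be compared and analyzed using the chi-squared test".

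Data analysis then assigns the distribution an outcome type: "For dichotomous outcomes, such as the percentage of BI ≥ 90, distribution of mRS scores". The same sentence goes on to name the test: "distribution of mRS scores, proportion of early neurological deterioration, and recurrence rate of stroke, we will use the chi-squared test", with Fisher's exact test as the alternative, used "to compare the distribution of patients between the two groups". The next sentence covers estimation: "Logistic regression is utilized to estimate the 95% CI". It does not name the kind of logistic model.

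A rank test does appear in the plan, but only for variables called continuous: "Student’s t-test or Wilcoxon rank-sum test is employed to analyze the differences between the two groups". The mRS is not in that list. No ordinal, shift or rank analysis is assigned to mRS anywhere in the article.

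**The concern.** A distribution over an ordered scale with more than two levels is not a dichotomous outcome, so the two sections cannot both be right. This is more than a detail left to the analysis plan: the article states an outcome type and a test, and neither suits the outcome it has defined.

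Reducing disability is the trial's stated aim, and this outcome is its measure of degree of disability. A reader would expect it to show whether patients moved towards better scores across the whole scale, and by how much. A test that ignores order does not answer that, and a second test at mRS ≤ 2 adds nothing at D90. If the choice is left open until the data are seen, a later ordinal analysis will look data-driven.

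**Working it through.** **Step 1. The two readings.**

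| Reading of Data analysis | What is tested | Consequence |
|---|---|---|
| Full distribution kept | 2 × 7 table if mRS runs 0 to 6; (2−1)(7−1) = 6 df | The Pearson statistic is unchanged if the columns are reordered, so it carries no direction |
| Taken literally as dichotomous | 2 × 2 table; the only outcome cut named for mRS is ≤ 2 | D90 repeats the primary; the distribution in Secondary outcomes is never analysed |

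Neither reading delivers what Secondary outcomes promises.

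**Step 2. Inputs.**
- From Sample size calculations: mRS ≤ 2 in 65% of controls and 76.5% of the intervention group; two-sided α 0.05; 240 per group; 20% dropout.
- Evaluable per arm: 240 × 0.8 = 192. Both 192 and 240 are used below, because the article also plans imputation and carry-forward.
- Assumed, because the article gives no full mRS distribution: seven levels (0 to 6) and four control distributions, each with 65% at mRS ≤ 2.

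**Step 3. The plan's own figures.** The article states no power for the mRS distribution, so there is none to reproduce. Its only design figure is for the primary. With p = (0.65 + 0.765)/2 = 0.7075, the printed formula gives 2 × 0.7075 × 0.2925 × (1.960 + 0.842)² / 0.115² = 246 per group before dropout. Power for the primary is then 79% with 240 evaluable per arm and 70% with 192. That the stated 240 does not also cover dropout is a separate matter, and this point does not rest on it.

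**Step 4. Implied shift.** Odds ratio = (0.765/0.235)/(0.65/0.35) = 3.255/1.857 = 1.753. Applied to every cumulative odds of one assumed control distribution:

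| mRS | 0 | 1 | 2 | 3 | 4 | 5 | 6 |
|---|---|---|---|---|---|---|---|
| Control p | .150 | .270 | .230 | .120 | .110 | .050 | .070 |
| Intervention q | .236 | .323 | .206 | .089 | .073 | .031 | .041 |

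**Step 5. Power of the full-table test by formula.** The noncentrality is λ = n Σ (p − q)²/(p + q). The sum is 0.0491, so λ = 9.42 at n = 192 and 11.78 at n = 240. A noncentral chi-squared with 6 df then gives 61% and 73%.

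**Step 6. Simulation.** 20,000 trials per setting, common odds ratio 1.753, range over the four control distributions:

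| Per arm | Full-table chi-squared | mRS ≤ 2 | Wilcoxon rank-sum |
|---|---|---|---|
| 192 | 60–62% | about 70% | 86–87% |
| 240 | 72–73% | 79–80% | about 93% |

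At odds ratio 1.0 all three tests reject in about 5% of trials. The cost of the extra degrees of freedom can also be seen directly: 80% power needs λ = 13.62 on 6 df and 7.85 on 1 df, and 13.62/7.85 = 1.74. With a smaller common odds ratio of 1.5, 192 per arm and one assumed control distribution (14/29/22/14/10/6/5%), power is 33%, 46% and 62% in the same order.

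**Step 7. Departures from a uniform shift.** 192 per arm, control distribution of Step 4, still 65% against 76.5% at mRS ≤ 2:

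| Pattern | Full-table chi-squared | mRS ≤ 2 | Wilcoxon |
|---|---|---|---|
| Each side of the 2/3 cut only rescaled | 41% | about 70% | 52% |
| All benefit is a move from 3 to 2 | over 99% | about 70% | 11% |

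The advantage of the ordinal test shrinks in the first case and reverses in the second.

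**The case against.** Four points can be made for the plan.

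1. The article never mentions a seven-column table. A reader might infer that a 6-df test is planned, but the text supports a literal 2 × 2 reading equally well, and the arguments about degrees of freedom and direction then fall away. This stands. What remains under that reading is the duplication of the primary at D90, the missing analysis of the distribution, and a smaller loss against an ordinal test: 87 − 70 = 17 points at 192 per arm and 93 − 80 = 13 at 240.

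2. The article says logistic regression, not binary logistic regression. A reader might infer that no common odds ratio can come out of this plan. The sentence follows the dichotomous list, which suggests a binary model but does not establish it, and the analysis plan is not shown. So the absence of an effect estimate cannot be asserted.

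3. The power gap depends on a common odds ratio, which the article does not assume. It gives only the two proportions at mRS ≤ 2. This stands, and Step 7 shows how far it matters. The move from 3 to 2 alone is an extreme case, and the primary already targets that cut; the reason to add a distribution is to see change elsewhere on the scale.

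4. The outcome is secondary and the trial is not sized on it. A reader might treat it as the main support for the primary, but the abstract and Discussion summarise the secondary outcomes without naming it.

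None of this removes the conflict between the two sections.

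**Conclusion.** The point holds as a conflict between two sections and an ill-suited analysis of one secondary outcome. The wrong outcome type, and the failure of either reading to deliver a directional analysis of the distribution, do not depend on any assumed effect.

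The size is conditional. With a common odds ratio of 1.753 and the assumed control distributions, an ordinal test gains about 25 points over a full-table chi-squared test at 192 per arm and about 20 at 240. A reader might conclude that the plan loses this power whatever the treatment does; the documents do not support that, because the gain rests on a broadly uniform shift. The primary test and type I error are not affected. It should be corrected, but it does not threaten the trial's main conclusion.

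**What to change.** Remove the mRS distribution from the dichotomous list in Data analysis. Prespecify one ordinal analysis for D30 and D90, in writing before unblinding: proportional-odds logistic regression, reporting the common odds ratio with its 95% CI, adjusted for baseline covariates already collected, such as NIHSS and age.

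Report the odds ratio at each cut-point, or a Mann-Whitney effect measure, as a fixed sensitivity analysis. Do not let a test of proportional odds decide which method is used; a switch of that kind makes the analysis depend on the data.

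The cost is a few sentences of plan text and no new data. The one drawback is interpretive: if proportional odds does not hold, the common odds ratio is an average effect over the cut-points, which is why the cut-point results should be shown beside it.

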### Trial population

Patients from 24 hospitals in 14 provinces in China were recruited for the study (Fig. 2). The detailed inclusion and exclusion criteria are listed in Table 1.

Recruitment posters will be posted at these hospitals, so that patients can learn about the study and contact researchers. Participants were screened according to screening criteria and informed of the risks and benefits of participating in the study, as well as the collection of blood samples.If patients agree to participate in the study, they will sign an informed consent form. Recruitment began in November 2023, with initial completion expected in December 2025.If there are very serious cases of toxic side effects or insufficient recruitment, the trial will be stopped.

**Table 1 Tab1:** Inclusion and exclusion criteria

• **Inclusion criteria** • Diagnosed as having acute ischemic stroke; • Large artery atherosclerosis ischemic stroke according to the TOAST classification; • Patients with acute ischemic stroke within 48 h of onset; • Patients aged 18–80 years; • Patients with NIHSS score of 4–18 points; • An average Systolic blood pressure at least 3 times ≤ 155 mmHg before the patient’s enrollment; • Being informed about the study and signing informed consent.	• **Exclusion criteria** • Patients who have received intravenous thrombolysis or intravascular treatment; • Posterior circulation infarction; • Stroke caused by tumors; • Previous history of stroke and mRS ≥ 2 points before the onset of this stroke; • NIHSS 1a > 2 points; • Patients with a yellow and greasy tongue layer; • Patients with other diseases that limit the evaluation of neurological function or affect patient follow-up; • Patients with severe abnormal liver and kidney function with serum ALT, AST, or SCr over two times the upper limit of the reference range; • Have another serious life-threatening illness with life expectancy of less than 3 months; • Pregnant, with recent family planning, or lactating women; • Currently participating in other interventional clinical trials.

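### Only unadjusted tests are named for the continuous secondary and exploratory outcomes, although four of them have a scheduled baseline value that an ANCOVA could use at almost no cost

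*Protocol article*

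**What the plan says.** The Data analysis section of the protocol article lists the continuous variables as neurological function, MMSE, PRO and cerebral blood flow measures, "such as changes from baseline to treatment endpoints", and states that Student's t-test or "Wilcoxon rank-sum test is employed to analyze the differences between the two groups". No regression model, baseline term or confidence interval is named for them. For the dichotomous outcomes, by contrast, logistic regression is named as the source of the 95% CI.

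Secondary outcomes fixes the form of each measure:

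- NIHSS is "measured by the change in the NIHSS scale between baseline and D10".
- The syndrome scale is a change assessed at baseline and D10. The Data analysis list does not name it, but its wording is not exhaustive.
- PRO is "measured by the change in the PRO scale between baseline and D10".
- MMSE is "evaluated using MMSE scores at D90", a final score and not a change.

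One sentence on adjustment appears: "The statistician will perform covariate adjusted analyses and covariate unadjusted analyses". It stands between the chi-squared test for mRS ≤ 2 and the list of subgroups, and it names neither covariates nor outcomes.

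Appendix C ticks NIHSS at screening, and MMSE, the syndrome evaluation scale and ASL on Day 1. ASL is done at 8 centres only. PRO has a single tick, at Day 10.

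**The concern.** Where a baseline value of the same measure exists, a two-sample test on the change fixes the slope of follow-up on baseline at 1, and a test on the final score fixes it at 0. ANCOVA estimates the slope from the data. Fixing it at a wrong value has two costs. The treatment difference is estimated with more variance than necessary, and a chance difference between the arms at baseline carries over into the estimate.

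At stake is the precision of the secondary efficacy results (NIHSS at D10, syndrome score at D10, MMSE at D90) and of the exploratory ASL flow. The last comes from a subset of centres, so precision is scarcer there and chance imbalance more likely. The baseline data for all four are already in the visit schedule, so the gain needs no further data collection.

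**Working it through.** **Inputs from the article.** Tests and outcome forms as above. Two-sided α of 0.05, power 80%, 240 per group and 20% dropout come from Sample size calculations, so 240 × 0.8 = 192 evaluable per arm. The article states no SD, correlation or power for any continuous outcome, so there is no figure of its own to reproduce here.

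**Assumed inputs.** Correlation r between baseline and follow-up of 0.3 to 0.9. Ratio k of follow-up SD (s1) to baseline SD (s0) of 0.8, 1.0 and 1.5.

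**Variance.** The per-arm variance entering the treatment difference is:

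- change score: s0² + s1² − 2·r·s0·s1
- ANCOVA (large samples): s1²·(1 − r²)
- raw final score: s1²

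Change score minus ANCOVA gives s0² − 2·r·s0·s1 + r²·s1² = (s0 − r·s1)². This is never negative, and it is zero only if r·s1 = s0, that is, if the true slope is 1. Final score minus ANCOVA gives r²·s1², also never negative.

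**Equal SDs (k = 1).** The ratio of ANCOVA to change score is (1 − r²)/(2(1 − r)) = (1 + r)/2. If the change-score t-test has 80% power, ANCOVA has power Φ(2.802·√(2/(1+r)) − 1.96). At r = 0.5 this is Φ(2.802 × 1.155 − 1.96) = Φ(1.28) = 0.899. At r = 0.7 it is Φ(2.802 × 1.085 − 1.96) = Φ(1.08) = 0.860. In numbers of patients, 192/0.75 = 256 and 192/0.85 = 226 per arm: the size a change-score analysis would need for the same precision.

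**Ratio of ANCOVA to change-score variance, with ANCOVA power where the change score has 80%:**

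| r | k = 0.8 | k = 1.0 | k = 1.5 |
|---|---|---|---|
| 0.3 | 0.50 (97.7%) | 0.65 (93.5%) | 0.87 (85.1%) |
| 0.5 | 0.57 (96.0%) | 0.75 (89.9%) | 0.96 (81.4%) |
| 0.7 | 0.63 (94.3%) | 0.85 (86.0%) | 1.00 (80.1%) |
| 0.9 | 0.61 (94.9%) | 0.95 (82.0%) | 0.78 (88.8%) |

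The reduction therefore runs from about 0 to 50%.

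**MMSE as a raw D90 score.** The ratio is 1 − r²: 0.91, 0.75, 0.51 and 0.19 at r = 0.3, 0.5, 0.7 and 0.9.

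**Chance imbalance.** Let d be the observed baseline difference between the arms and b = r·s1/s0 the true slope. Given d, the change-score estimate is off by (b − 1)·d and the raw final score by b·d. With equal SDs, b = r. One point of imbalance in NIHSS then shifts the change-score estimate by −0.5 points at r = 0.5 and by −0.3 at r = 0.7. Over repeated randomisation the average of d is zero, so the average shift is zero too.

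**The case against.** The strongest reply is that nothing here is an error. In a randomised trial a two-sample test on changes or final scores controls the type I error and is unbiased over randomisation. That stands. A reader might infer from the carry-over of baseline imbalance that the planned comparison is biased or invalid. It is not: the shift is an error conditional on the imbalance that happens to occur.

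A second reply is that covariates for secondary models belong in a statistical analysis plan, and that the sentence on adjusted analyses may already cover these outcomes. The wider reading cannot be excluded. But the sentence sits with the primary test, and the next paragraph gives the continuous outcomes their own unadjusted tests. The article thus states a choice of method and does not merely leave one open.

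Third, the gain may be small. Entry requires "Patients with NIHSS score of 4–18 points", which limits the spread of baseline NIHSS but not of later scores, so a follow-up SD above the baseline SD is plausible. At k = 1.5 and r near 0.7 the gain disappears. This stands, and it rules out quoting the equal-SD figures as the expected loss. The variance formulas also describe the t-test only; they say nothing exact about the Wilcoxon test, which the plan equally allows and which may do well with strongly skewed scores.

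Two further inferences go beyond the text. One is that every continuous outcome is a change score: MMSE is defined as the D90 score. The other is that ANCOVA can be applied to all of them at once: as scheduled, PRO has no baseline, so neither a change nor an ANCOVA is possible. It remains possible that the table lost a tick when it was read.

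**Conclusion.** The point holds as a free improvement, not as a flaw in validity. For NIHSS, the syndrome scale, MMSE and ASL flow, the article names only unadjusted tests although a baseline value is scheduled. In large samples ANCOVA is never less precise than a t-test on the change or final score, and it removes the conditional effect of chance baseline imbalance.

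The size cannot be computed from the article. With equal SDs the variance falls by 25% at r = 0.5 and 15% at r = 0.7. Across the assumed range the fall is about 0 to 50% against a change score, and r² against a raw D90 MMSE score. All of these rest on assumed correlations and SD ratios and on 1:1 allocation with a common slope.

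Only secondary and exploratory outcomes are concerned. A reader should not carry the power figures over to the trial as a whole: the mRS ≤ 2 comparison and the 480 patients are not touched.

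**What to change.** Before the first level of unblinding, state in the analysis plan that the main analysis of NIHSS at D10, the syndrome evaluation scale at D10, MMSE at D90 and ASL flow at D10 is an ANCOVA of the post-treatment value on treatment and its own baseline value. Include centre, because Study design makes it the randomisation stratum; the article describes no primary model with centre to borrow from. Report the adjusted mean difference with its 95% CI. Keep the Wilcoxon test or a rank-based ANCOVA as the sensitivity analysis for skewed scores. Say explicitly which outcomes the sentence on adjusted and unadjusted analyses covers.

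PRO can be treated in the same way only once Secondary outcomes (change from baseline) and Appendix C (Day 10 only) are reconciled.

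The cost is a few lines of wording. No visit, measurement or patient is added for the four named outcomes.
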